### Outcome assessment

The data presented in Table 2 will be measured before the operation and 3 and 12 months postoperative. Physical function and DXA scan will be measured during clinic visits. All the self-reported questionnaires are send by e-mail or post to the patients 2 weeks before the visit together with the tri-axial accelerometer. The primary outcome measure of the study is the 100-mm Visual Analogue scale (VAS), which is a self-reported pain measurement ranging from 0 indicating “no pain” to 100 indicating “worst pain imaginable” [31].

**Table 2 Tab2:** Primary and secondary outcome measures

Measure	Instrument	Collection points and method
Primary outcome:		
Self-reported Pain intensity	Visual Analogue Scale (VAS)	Baseline, 3 and 12 months follow up by post/email
Secondary outcomes:		
Self-reported function	SF-36 Physical Function	Baseline, 3 and 12 months follow up by post/email
Self-reported function and pain	Oxford Knee Score (OKS)	Baseline, 3 and 12 months follow up by post/email
Self-reported health status	EQ-5D-3 L	Baseline, 3 and 12 months follow up by post/email
Self-reported pain catastrophizing	Pain Catastrophizing Scale (PCS)	Baseline, 3 and 12 months follow up by post/email
Self-reported daily function and quality of life	Knee injury and Osteoarthritis Score (KOOS)	Baseline, 3 and 12 months follow up by post/email
Self-reported pain self-efficacy	Pain Self-Efficacy Questionnaire (PSEQ)	Baseline, 3 and 12 months follow up by post/email
Daily activity	Tri-axial accelerometer	Baseline, 3 and 12 months follow up by post/email
Physical function	6 min’ walk test (6MWT)	Baseline, 3 and 12 months follow up test in clinic
Physical function	Sit to stand 30 s. (STS30)	Baseline, 3 and 12 months follow up test in clinic
Muscle mass and bone mineral density	DXA scan	Baseline, 3 and 12 months follow up scan in clinic
Other measures		
Healthcare visits	Self-report (log book)	0–3 months’ post-operative at home
Smoking	Self-reported questionnaire	Baseline, 3 and 12 months follow up by post/email
Pain killers	Self-reported questionnaire	Baseline, 3 and 12 months follow up by post/email
Alcohol	Self-reported questionnaire	Baseline, 3 and 12 months follow up by post/email
Education	Self-reported questionnaire	Baseline, 3 and 12 months follow up by post/email
Social status	Self-reported questionnaire	Baseline, 3 and 12 months follow up by post/email

Secondary outcomes will be several self-reported questionnaires: SF-36 (physical function) [32], Oxford Knee Score (OKS) [33], EQ-5D [34], Pain Catastrophizing Scale (PCS) [28], Knee injury and Osteoarthritis Score (KOOS) [35] and Pain Self-Efficacy Questionnaire (PSEQ) [36–38]. Daily activity will be measured over 7 days with tri-axial accelerometers [39, 40]. Two performance-based measures, the 6-minute walk test [41, 42] and sit to stand on 30 s [43–45] will be assessed to measure Physical function. The performance tests are supervised by a trained staff following a SOP to insure standardization. Muscle mass and bone mineral density (BMD) will be measured with a DXA scan and the patients are asked to record health care visits after the operation in a logbook. Other measures collected with self-reported questionnaires are smoking, alcohol, work, education, use of pain killers and social status. Further information about comorbidity, operation, complications, rehabilitation and previous knee surgery will be registered by medical records.

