### Exclusion criteria

Severe depression (at least three core symptoms and two accompanying symptoms) diagnosed with the Major Depression Inventory (MDI) [26].Scheduled for revision arthroplasty.Scheduled for a unicompartmental arthroplasty.Planning to have a contralateral knee arthroplasty within 1 year from the operation.Have a diagnosis of inflammatory arthritis.

Patients eligible for participation will be randomized into the two arms, usual care or patient education (Fig. 2). The patients will not be aware of the study hypotheses and will not be informed about the association between a high PCS score and long-term pain after TKA. The randomization will take place approximately 2–3 weeks before the operation. Because the time between the patients are scheduled for operation by the surgeon and the operation is very short (2–3 weeks) the patients will be randomized immediately after they are included and before baseline assessments to be able to make three pre-operative appointments with the patients in the intervention group.

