### Preoperative screening and selection of “high Pain Catastrophizing” patients

Patients will be screened preoperatively at the outpatient clinic after they are scheduled for a TKA using the questionnaire Pain Catastrophizing Scale (PCS) [27]. PCS consists of 13 questions where the patients rate their thoughts and feelings when they are experiencing pain. The total score is ranging from 0 indicating no “pain catastrophizing” to 52 indicating worst “pain catastrophizing”. Each item are rated on a 5-point scale ranging from “not at all” to “all the time”. The Danish version of PCS is considered valid for use in clinical pain samples and the internal consistency is found acceptable [28].

The cut-off score for PCS is chosen on basis of data collected in the years 2011–2013 at Holstebro Regional Hospital. 530 TKA patients answered the PCS before the operation. Median PCS score was 16 range (0–52). In the present trial we want to include the 33% of our TKA population with the highest PCS score. This means that we will use the 66th percentile of the total score to define the cut-off in this study. Thus, patients with a PCS score on 23 or higher are eligible for inclusion and in this study defined as patients with “high pain catastrophizing”.

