### Intervention group

The intervention group will in addition to the described usual care participate in a patient education based on cognitive-behavioral therapy. We wanted to design a patient education that fits into a hospital setting with relatively few session contrary to previous studies were the CBT intervention most commonly range from 10 to 12 sessions [20, 23, 29]. Our patient education consists of seven individual sessions. Three sessions before the operation and four after. A similar trial has recently shown similar amounts of sessions to be effective [24]. Except session one and three all the sessions will be in relation to the above mentioned planned visits at the hospital. The first session will be delivered approximately 2 weeks before the operation and the last one 3 months after the operation. Each session will be approximately 45 min in length. The patient education will be delivered by one of three physiotherapists with several years of experience in treating patients with TKA and a special interest in the CBT area. The three physiotherapists have participated in a 3-day training program delivered by two psychologists specialized in cognitive behavioral therapy and pain management. The patient education is developed together with the two psychologists and the three physiotherapists. The intervention is pilot tested on 3 patients with high pain catastrophizing score before we started including patients.

The same physiotherapist will follow the patient through all the 7 sessions. To make sure that the physiotherapists will all deliver the intervention in the same way they will be observed by each other on a regular basis.

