There are some limitations as well. First, due to the different amount of attention paid to the patients in the two groups, a Hawthorne effect is possible [50, 51]. However, all patients will receive at least standard care which includes several contacts to both nurses, physiotherapists and doctors. Second, DXA scan, 30 s sit-to-stand and 6 MWT will be conducted after the first session in the intervention group. This procedure is chosen to be able to maintain the blinding of the physiotherapists by testing all the patients in the two groups the same day. However, the content of the first session is mostly introduction and since these outcome measures are not patient reported we do not think this will have an impact upon the results. Third, the patients will be randomized before baseline assessment. The reason for this is that the time between the patients are referred to a TKA and the operation is short and to be able to see the patients in the intervention group three times before the date for the operation this procedure is chosen. However, none of the patients are informed about the association between a high PCS score and long-term pain after TKA, so we don’t think this will affect the results.

We consider the external validity of the trial to be high while the treatment of TKA patients is almost similar all over the country. This makes it easier to implement at other Hospitals.

This project is expected to improve the overall treatment effect for a group of patients we today do not know how to treat the best way. We hope that this study can provide better functional outcome and less pain for the patients after the operation and that the study can produce new knowledge and inspire similar developments of interventions to other diseases.

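### For most of the stated 2–3 week wait, the baseline accelerometer dispatch rule does not fit the schedule, and a 7-day baseline recording runs past session 1 in the intervention arm only

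*Protocol article*

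**What the plan says.** **Entry and randomisation.** Screening takes place only once surgery is booked: "Patients will be screened preoperatively at the outpatient clinic after they are scheduled for a TKA". The Exclusion criteria section puts the interval from booking to operation at 2–3 weeks and adds: "The randomization will take place approximately 2–3 weeks before the operation". On the order of events, it says that "the patients will be randomized immediately after they are included and before baseline assessments".

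**Dispatch and recording.** The Outcome assessment section gives one rule for all time points: "All the self-reported questionnaires are send by e-mail or post to the patients 2 weeks before the visit together with the tri-axial accelerometer". It also says: "Daily activity will be measured over 7 days with tri-axial accelerometers". The day on which wear starts is not given.

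**Intervention.** The Intervention group section says: "The first session will be delivered approximately 2 weeks before the operation". Table 1 puts session 2 at 1 week and session 3 at 3–5 days before surgery.

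**Baseline clinic tests.** Among its limitations, the Discussion says that "DXA scan, 30 s sit-to-stand and 6 MWT will be conducted after the first session in the intervention group". The accelerometer is not on that list. The day of the baseline visit is not stated. The only planned preoperative hospital contact in usual care is the information meeting, about 1 week before surgery (Control group section).

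**Analysis.** The Sample size and statistical analysis section estimates group differences in pain from baseline to each follow-up with a mixed model. Normally distributed secondary outcomes are handled the same way.

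**The concern.** Two timing problems sit side by side. A kit that must leave two weeks before a visit, when that visit follows session 1 at about day -14, would often have to be sent before the patient has been included. And a recording that takes seven days has at most about a week between inclusion and session 1 in which to run.

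The consequence differs by arm. The baseline week is untreated in controls. In the intervention arm it may lie partly or wholly after the education has begun, by an amount that depends on each patient's wait. Physical activity is a named secondary aim, and raising activity is one of the things the education tries to do. With effects measured from baseline, any activity change already present in the baseline week is removed from the estimated effect.

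**Working it through.** Day 0 is the operation. The article gives no figure of its own to reproduce, so this is a count of days.

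**Inputs**
- Wait W from inclusion to operation: 14 to 21 days, so inclusion is on day -W (Exclusion criteria; screening section).
- Session 1: about day -14 (Intervention group; Table 1).
- Baseline visit on day V: after session 1 and before surgery (Discussion). V = -7 is an inference from the information meeting.
- Dispatch: day V - 14 (Outcome assessment).
- Recording: 7 days (Outcome assessment).
- Postal lag L: not stated; taken as 0 to 2 days.

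**Step 1: can the dispatch rule be met?** It needs V - 14 ≥ -W, that is, W ≥ 14 - V.

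| Visit day V | Dispatch due | Shortest wait that allows it |
|---|---|---|
| -7 | -21 | 21 days |
| -5 | -19 | 19 days |
| -3 | -17 | 17 days |
| -1 | -15 | 15 days |

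At W = 14 no preoperative visit day works; even V = -1 needs dispatch on day -15, one day before inclusion. At V = -7 dispatch is due 7 days before inclusion for a 14-day wait, 4 days before for 17 and 2 days before for 19.

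**Step 2: how much of the recording follows session 1?** This ignores the dispatch rule and takes the earliest possible start, day -W + L. The recording ends at -W + L + 7, so the days after session 1 are min(7, max(0, 21 - W + L)).

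| Wait W | L = 0 | L = 2 |
|---|---|---|
| 14 | 7 | 7 |
| 16 | 5 | 7 |
| 18 | 3 | 5 |
| 20 | 1 | 3 |
| 21 | 0 | 2 |

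**Step 3: does a later visit help?** It makes the rule feasible at shorter waits but delays the device. For a 21-day wait with no lag, following the rule with V = -7 starts wear on day -21 and leaves 0 days after session 1. With V = -5 wear starts on day -19 and leaves -19 + 21 = 2 days. With V = -1 it starts on day -15 and leaves -15 + 21 = 6 days.

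**Step 4: which sessions can fall in the week?** At a 14-day wait with no lag, wear runs from day -14 to -7 and ends about when session 2 takes place. With a 2-day lag it runs from day -12 to -5, past session 2 and up to the edge of session 3 (days -5 to -3).

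**Step 5: sensitivity to session 1.** If session 1 slips to day -12, the no-lag overlap is 5 days at a 14-day wait, 2 at 17 and 0 at 21. With a 2-day lag it is 7, 4 and 0.

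**Step 6: effect on the estimate.** If the education shifts mean activity by x on days after session 1, and d of 7 recorded days fall there, the intervention-arm baseline moves by (d/7)x and the change contrast by the same amount in the opposite direction. With no lag that is x at a 14-day wait, 3/7 = 0.43x at 18 days and 0 at 21 days. The documents give no value for x.

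**The case against.** Much can be said in the plan's favour. The times are given as approximate, the baseline visit day is inferred, and the dispatch sentence is a general one covering three time points in a condensed article. Session 1 is mainly introduction. Table 1 brings in the relation between activity and pain only in session 2 and pacing only in session 3, so even a recording wholly after session 1 may contain few or no days after any activity content. The Discussion already admits that some baseline measures follow session 1, and part of its defence, that they are not patient reported, fits an accelerometer too.

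These points limit the finding, and they rule out three stronger readings that a reader might infer:

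- *That the rule can never be met.* It can be met at a full 3-week wait, or at a somewhat shorter one if the visit is later than day -7.
- *That the dispatch rule causes the overlap.* The overlap comes mainly from the gap of about 0–7 days between inclusion and session 1, and would remain if the rule were dropped.
- *That the activity result is shown to be biased.* Neither the size nor the direction of any early change is known.

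What stands is that the stated times conflict over most of the stated wait. The Discussion's defence was also written for single-day clinic tests. It does not address a week of free-living behaviour that can extend to later sessions.

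**Conclusion.** The point holds in a limited form. At a 14-day wait the dispatch rule fits no preoperative visit day, and with a visit at about day -7 it fits only a 21-day wait. With the earliest possible start and no postal delay, about 7, 3 and 0 of the 7 baseline days follow session 1 at waits of 14, 18 and 21 days, in the intervention arm only. At short waits, postal delay or later dispatch can carry the recording to session 2 or 3.

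The dispatch conclusion at waits of 15 to 20 days rests on the inferred day -7 visit. The overlap count does not; it rests on session 1 at about day -14 and on the stated wait. The consequence is a possible distortion of unknown size in one secondary outcome. The same dispatch sentence governs the baseline questionnaires, including the pain VAS, but they need no seven-day recording and the article does not say when they are completed, so the overlap count does not carry over to the primary outcome.

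**What to change.** 1. Reconcile the statements on inclusion, session 1, dispatch, the 7-day recording and the baseline clinic tests (Exclusion criteria, Intervention group, Outcome assessment, Discussion), so that the baseline wear window is stated relative to session 1.
2. For baseline only, replace posting with handing out the accelerometer at the clinic on the day of inclusion. Start recording that day, and record for each patient the number of valid days before session 1.
3. Keep the planned analysis from baseline, and add a sensitivity analysis that compares daily activity at 3 and 12 months directly between arms without subtracting baseline.
4. Add the accelerometer to the Discussion's list of measures taken after session 1.

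The cost is a change in logistics and a few sentences. At a 2-week wait few or no days precede session 1, so the hand-out does not clear the overlap there; the sensitivity analysis is the safeguard for those patients. That comparison may be less precise because it does not use baseline activity, which is why it should supplement the planned analysis and not replace it.

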### Sample size and statistical analysis

The primary outcome measure will be VAS under activity measured on a continuous 100 mm scale 12 month after the operation. Clinically important differences between the two groups is detected to be 18 mm [46, 47]. Based on earlier studies we assume a common standard deviation between participants of 19 mm on VAS [2, 10, 48]. With a significance level at 0.05 and the power at 0.90 the study needs 23 patients in each arm. Taking into account a loss to follow-up after 1 year on approximately 20% we aim at including 28 patients in each group a total of 56 patients.

Clinical and demographic characteristics as well as baseline data will be presented to show the baseline comparability of the two groups. Data from the patients who withdraw from the study will also be examined. For each group descriptive statistics will be presented at baseline and three and 12 months postoperative. Normally distributed data are described by means and standard deviation (SD), and data not normally distributed by medians and interquartile range (IQR). The primary analysis will use the intention-to treat principle including all randomised participants. Patients who discontinue the intervention will be encouraged to participate in the follow up test anyway, and those who accept will be included in the analyses according to their original group assignment. The primary outcome pain is measured on a continuous scale and between-group mean differences and 95% confidence intervals from baseline to 3 and 12 months will be analyzed by a mixed effects linear regression model with a random person level and systematic effects of time, group and the interaction between time and group. We will employ multiple imputation methods in order to assess the sensitivity of the mixed model to any informative missing values. Imputations will be performed using baseline characteristics and non-missing pain measurements on individual levels. Secondary outcomes will be analysed as above for normally distributed measures or for binary outcomes, we will use logistic regression with a robust variance estimate to account for the repeated measurements. Standard diagnostic plots will check model assumptions. The statistical analyses will be performed using STATA 13 (StataCorp, College Station, TX) software package. The significance level will be set at 0.05.

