
## Methods/Design

### Design

This study is a single centre double-arm parallel group design trial with 1:1 allocation with 1-year follow-up. Measurements will be taken at baseline before the operation and 3 and 12 months after the operation.

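### The stated 23 per arm falls just short of 90% power, and 28 per arm does not leave 23 after a 20% loss; the shortfall is about 1 to 3 power points

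*Protocol article*

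**What the plan says.** The calculation is in the protocol article under Sample size and statistical analysis. The outcome is VAS pain under activity 12 months after surgery.

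- Difference: "Clinically important differences between the two groups is detected to be 18 mm".
- Variability: "we assume a common standard deviation between participants of 19 mm on VAS".
- Requirement: "With a significance level at 0.05 and the power at 0.90 the study needs 23 patients in each arm".
- Loss allowance and target: "Taking into account a loss to follow-up after 1 year on approximately 20% we aim at including 28 patients in each group", which makes 56 in total.

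The Design section gives equal allocation: "double-arm parallel group design trial with 1:1 allocation with 1-year follow-up". The level is repeated at the end of the statistical section: "The significance level will be set at 0.05". The article does not say whether the test is one- or two-sided, which formula was used, or how 28 was obtained from 23. The 90% is attached to the 23 patients needed per arm, before the loss allowance.

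**The concern.** Two steps each come out slightly on the favourable side. First, a required sample size is rounded up, because rounding down leaves power below target; 23 appears to be 23.4 rounded down. Second, an allowance for loss should leave the required number once the loss has occurred, and 28 per arm does not leave 23 if 20% are lost.

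What is at stake is the accuracy of the stated power and requirement. A reader weighing an inconclusive result from 56 patients would take the trial to have had 90% power for 18 mm after the expected loss. On the plan's own inputs it has a little less.

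**Working it through.** **Inputs (protocol article).** Difference δ = 18 mm, SD σ = 19 mm, α = 0.05, power 0.90, loss about 20%, 28 per arm (Sample size and statistical analysis); allocation 1:1 (Design). Two-sided testing is my assumption: it gives a result next to the stated 23, whereas a one-sided normal calculation gives 20.

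**Step 1: reproduce the 23.**

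n per arm = 2 × (z₀.₉₇₅ + z₀.₉₀)² × (σ/δ)² = 2 × (1.960 + 1.2816)² × (19/18)² = 23.41

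This is the plan's 23 before rounding. Rounded up it is 24. With the noncentral t distribution the solution is 24.42, so 25.

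**Step 2: power by evaluable patients per arm.** The normal approximation is Φ(δ / (σ√(2/n)) − 1.960). For n = 23 this is Φ(3.213 − 1.960) = Φ(1.253) = 0.895.

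| Evaluable per arm | Normal | t-test |
|---|---|---|
| 22 | 88.1% | 86.6% |
| 22.4 | 88.7% | 87.3% |
| 23 | 89.5% | 88.1% |
| 24 | 90.7% | 89.5% |
| 25 | 91.8% | 90.7% |

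So 23 per arm misses 90% narrowly under either formula. The normal formula reaches it at 24, the t-test at 25.

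**Step 3: the loss allowance.** This step needs no choice of power formula.

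- Remaining after 20% loss: 28 × (1 − 0.20) = 22.4, below the plan's own 23.
- Enrolment needed to keep 23: 23 / 0.80 = 28.75, so 29 per arm (58 in total).
- Largest loss at which 28 still leaves 23: 1 − 23/28 = 17.9%, that is 5 of 28. Losing 6 of 28 (21.4%) leaves 22.
- 23 × 1.2 = 27.6 rounds to 28, so the target is consistent with multiplying by 1.2. The article does not show its method.

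**Step 4: both steps together.**

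- Normal: 24 / 0.80 = 30 per arm, 60 in total.
- t-test: 25 / 0.80 = 31.25, so 32 per arm, 64 in total.
- Planned: 28 per arm, 56 in total. At 22 to 22.4 evaluable per arm, power is 88.1% to 88.7% (normal) or 86.6% to 87.3% (t-test).

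**The case against.** The strongest reply is that nothing material is wrong. At 23 per arm the normal approximation, which seems to be what was used, gives 89.5%, and that rounds to 90%. The loss step alone costs one patient per arm. The loss is given only as approximate, and 17.9% can pass for about 20%. The SD is itself an assumption taken from earlier studies, so a gap of 1 to 3 points lies within the uncertainty of the inputs.

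Much of this stands, and it is why the point is minor. It does not make the figures right: 23.4 rounds up to 24, and an approximate 20% covers losses above 20% as well as below.

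Three stronger readings are tempting, and the article does not support them:

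- **That power is 87%, not 90%.** A reader might infer this single figure, but it is the t-test result. The normal formula gives 88.1% to 88.7% after the same loss. The stated 90% also belongs to 23 evaluable patients, so setting it directly against an after-loss figure mixes two bases.
- **That 23 was multiplied by 1.2.** This fits, but no calculation is shown. Only the shortfall at 20% loss is established.
- **That the planned analysis has this power, or less.** The primary analysis is a mixed model on baseline, 3-month and 12-month VAS, in which patients lost by 12 months can still contribute earlier data. Its power could be higher or lower than the two-sample figure. For illustration only, with 22.4 per arm, the t-test and 19 mm as the SD of a single measurement: an assumed baseline-to-12-month correlation of 0.3 to 0.5 gives 90.1% to 94.7% for a baseline-adjusted comparison and 74.5% to 87.3% for a change-from-baseline comparison. The article gives no correlation, so the model neither rescues the stated figure nor shows a larger loss. How the contrast is defined is a separate question.

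**Conclusion.** The sample-size statement is wrong as written, by a small amount. The 90% requirement is 24 evaluable patients per arm by the normal formula or 25 by the t-test, not 23. The target of 28 per arm leaves 22.4 after a 20% loss, short of the plan's own 23. With 56 randomised, a two-sample comparison at 12 months has roughly 87% to 89% power after about 20% loss, which is about 1 to 3 points below 90%.

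This rests on a two-sided test at 0.05, the stated 18 mm and 19 mm, equal arms, a full 20% loss, and an analysis of patients observed at 12 months. It does not call the design or the planned analysis into question.

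**What to change.** Keep 56 patients and restate the figures. For example: with a two-sided level of 0.05, a difference of 18 mm and an SD of 19 mm, 90% power needs 24 evaluable patients per arm (normal formula) or 25 (t-test); 56 patients will be randomised; with about 20% loss, about 22 per arm will be evaluable, giving roughly 87% to 89% power, depending on the formula, for a two-sample comparison at 12 months.

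Name the sidedness and the formula, and quote one power figure to match. If power is to be claimed for the mixed model instead, give the assumed within-patient correlation and its source.

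The cost is a few words and a slightly less favourable stated power. Enrolment, design and analysis do not change.

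### The primary estimate reads as a difference in change from baseline, but the sample size uses an SD for the VAS value itself, so the stated 90% power is unsupported for that contrast

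*Protocol article*

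**What the plan says.** All the key statements stand in the protocol article, under Sample size and statistical analysis.

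- Outcome: "The primary outcome measure will be VAS under activity measured on a continuous 100 mm scale 12 month after the operation".
- Target difference: "Clinically important differences between the two groups is detected to be 18 mm".
- Variability: "we assume a common standard deviation between participants of 19 mm on VAS".
- Size: "With a significance level at 0.05 and the power at 0.90 the study needs 23 patients in each arm". After an allowance for "loss to follow-up after 1 year on approximately 20% we aim at including 28 patients in each group a total of 56 patients".
- Primary estimate: "between-group mean differences and 95% confidence intervals from baseline to 3 and 12 months will be analyzed by a mixed effects linear regression model".
- Model: "with a random person level and systematic effects of time, group and the interaction between time and group".

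Table 2 (Outcome assessment) lists VAS at baseline, 3 and 12 months, so baseline VAS is one of the repeated measurements in the model. No baseline covariate is named, and the group means are not constrained to be equal at baseline. The sample-size text mentions neither change from baseline nor a correlation between visits.

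**The concern.** The trial appears to be sized on one quantity and analysed on another. In a model with free time, group and time-by-group effects, the between-group contrast running from baseline to 12 months is the interaction term, which is a difference in changes. Its variance includes the noise of the baseline measurement, and how much of that noise cancels depends on rho. The sample size is that of a plain comparison of two groups on a single VAS value.

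At stake is the width of the primary confidence interval in a trial of 56 patients with little reserve. If rho is low, the interval is wider than the design assumed, although the same data would support a tighter estimate. The same fitted model also yields the 12-month group difference. Unless one of the two is named as primary, the choice could be made after the baseline imbalance has been seen.

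**Working it through.** **Inputs from the protocol article:** difference 18 mm; SD 19 mm; alpha 0.05 (taken as two-sided, since sidedness is not stated); power 0.90; 23 per arm; about 20% loss; 28 per arm randomised 1:1.

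**Assumptions, not in the document:** SD of 19 mm at both baseline and 12 months; rho varied from 0.1 to 0.6.

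**Step 1. Reproduce the stated size.** For two means, n per arm = 2 × [19 × (1.960 + 1.282) / 18]² = 23.4. This agrees with the stated 23 apart from rounding. At 23 per arm the power is 0.895 by the normal approximation and 0.881 by the noncentral t. The stated size is therefore that of a comparison of VAS values with SD 19 mm.

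**Step 2. Completers.** 28 × 0.8 = 22.4, taken as 22 per arm. The matched 12-month comparison (SD 19 mm, two-sided t-test) then has power 0.866, or 87%. This is the benchmark for the table below.

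**Step 3. SD of each contrast.**
- Change from baseline: 19 × √(2(1 − rho)).
- 12-month value, unadjusted: 19 at any rho.
- 12-month value adjusted for baseline: 19 × √(1 − rho²).

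**Step 4. Power with 22 per arm** (difference 18 mm, noncentral t, two-sided 0.05; the one degree of freedom spent on the covariate is ignored).

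| rho | SD of change (mm) | Power, change | Power, 12-month unadjusted | SD adjusted (mm) | Power, 12-month adjusted |
|---|---|---|---|---|---|
| 0.1 | 25.5 | 63% | 87% | 18.9 | 87% |
| 0.2 | 24.0 | 68% | 87% | 18.6 | 88% |
| 0.3 | 22.5 | 74% | 87% | 18.1 | 90% |
| 0.4 | 20.8 | 80% | 87% | 17.4 | 92% |
| 0.5 | 19.0 | 87% | 87% | 16.5 | 94% |
| 0.6 | 17.0 | 93% | 87% | 15.2 | 97% |

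The variance ratio of change to adjusted is 2(1 − rho)/(1 − rho²) = 2/(1 + rho): 1.82 at rho 0.1 and 1.33 at rho 0.5.

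**Step 5. Where the two contrasts cross.** Setting SD_baseline² + SD_12m² − 2 × rho × SD_baseline × SD_12m equal to SD_12m² gives rho = SD_baseline/(2 × SD_12m). With equal SDs this is 0.5. With a 12-month SD of 19 mm and an illustrative baseline SD of 15 mm it is 15/38 = 0.39; with 25 mm it is 25/38 = 0.66.

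**Step 6. Does the mixed model rescue the change contrast?** It keeps partial data from patients lost to follow-up. With 28 per arm at baseline, 22 at 12 months, an equal correlation between all visits and a normal approximation, the change contrast has power of about 69% at rho 0.1, 79% at 0.3 and 90% at 0.5. The 12-month contrast from the same model has about 88 to 90%. The gap between the two contrasts therefore remains below rho of about 0.5.

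**The case against.** A difference in change from a longitudinal mixed model is a conventional analysis. The mismatch by itself neither biases the estimate nor inflates the type I error. The article is condensed, and an analysis plan that is not shown may fix the contrast. The phrase about baseline to 3 and 12 months might also be meant only to list the visits covered. These points limit the finding without removing it. The article states both the basis of the sample size and the estimate, and as written they do not match. If the 12-month difference was intended, the sentence still needs correcting.

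A reader might infer more: that the trial is underpowered, or that its primary interval will be wider than planned. The document does not support this, for four reasons.

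- It gives no correlation. That surgery between the two measurements makes rho low is plausible but is not evidenced here, and at rho 0.6 the change contrast does better than the unadjusted 12-month comparison.
- The threshold of 0.5 requires equal SDs at the two visits, and no baseline SD is given.
- The 19 mm is not labelled as a 12-month SD. That reading follows from the outcome definition just before it.
- The 87% at rho 0.5 contains no loss from using change. The matched 12-month comparison has the same 87%, because of the t-test and 22 completers.

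A further fair objection concerns baseline adjustment. Patients are randomised before baseline assessment (Exclusion criteria; Discussion, limitations), so the baseline VAS is recorded after randomisation in patients who are not blinded. This is a small drawback of using it as a covariate. Subtracting it, as the change contrast does, relies on the same value at full weight.

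**Conclusion.** The point holds as a mismatch between the estimate and the sample size. The stated 90% power is supported for a comparison of 12-month VAS values, apart from the small shortfall in the working, and is unsupported for the difference in change that the analysis sentence describes. It has not been shown to be missed.

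The size depends on an unstated rho. With 19 mm at both visits and 22 completers per arm, the change contrast loses about 24 percentage points of power against the unadjusted 12-month difference at rho 0.1 (63% against 87%) and about 13 at rho 0.3 (74% against 87%). It loses nothing at 0.5 and gains about 6 points at 0.6 (93% against 87%). Under the same assumptions, baseline adjustment has higher power than the change contrast at every rho in the table.

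**What to change.** State that the primary estimate is the between-group difference in VAS at 12 months from the mixed model. This matches the stated outcome and the sample size, and it needs only one sentence, with no new data or patients.

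Preferably, model the 3- and 12-month values with the baseline VAS already collected, and the screening PCS, as covariates, so that baseline is adjusted for and not subtracted. Because that VAS follows randomisation, also report the 12-month difference adjusted only for the pre-randomisation screening PCS, as a sensitivity analysis in all patients. A new pre-randomisation VAS is not needed, and the primary analysis should not be split according to which patients have which baseline data.

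If change from baseline is kept as primary, give the assumed SD of change, or the correlation together with both visit SDs, and restate the power for that contrast.
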